**Fig. 2 Fig2:**
[figure not shown]
Timeline of study visits. Deep brain stimulation (DBS) group: treatment with DBS of the subthalamic nucleus and best medical treatment (BMT). BMT group: treatment with BMT

### Statistics

#### Sample size calculation

The sample size calculation is based on the primary outcome measure. Given the (cognitive) vulnerability of the study population and as it is unknown whether the improvement in motor symptoms can outweigh the possible deterioration in cognition, a relatively large between-group difference in favor of DBS is needed to justify the use of DBS. An improvement of 15 points on the MDS-UPDRS part III in the off-drug state is assumed to be minimally clinically important. Therefore, a sample size of 17 patients in each group (34 patients in total) will have 80% power to detect a difference in mean change scores of 15 points on the MDS-UPDRS part III, assuming that the common standard deviation is 15, using a two-group t-test with a 5% two-sided significance level. Anticipating a 20% attrition rate, 22 patients per treatment arm will be included (44 patients in total).

For the main secondary objectives, the sample size has enough power only to detect large between-group differences in proportions of cognitive and psychiatric problems. Assuming a proportion of 10% of patients in the BMT group fulfilling the criteria for the composite outcome measure, a Fisher’s exact test with a 5% two-sided significance, will have 80% power to detect a difference of 49% between the DBS and BMT group when the sample size in each group is 17.

#### Statistical analysis

We will prepare a detailed statistical analysis plan before the database is finalized and locked. The statistical analyses will be based on the intention-to-treat principle. Baseline characteristics will be summarized using descriptive statistics. In all analyses statistical uncertainties will be expressed in 95% confidence intervals. A two-sided p-value < 0.05 will be considered statistically significant. The primary outcome - the MDS-UPDRS part III score in off-drug phase at week 30 - will be analyzed using the two-group t-test, assuming normal distribution. Additionally, the treatment effects on the MDS-UPDRS follow-up scores will be analyzed, using multivariable linear regression, including the baseline MDS-UPDRS scores into the model.

For the main secondary outcome, a composite dichotomous outcome measure will be used. The difference in the proportion for the dichotomous composite outcome measure between the DBS and BMT group will be analyzed using the chi-squared test or Fisher’s exact test, when appropriate. For the other secondary outcomes, we will use the appropriate parametric and nonparametric statistics to compare the DBS group and the BMT group for normally and not-normally distributed data, respectively.

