**Methods:**

A single center, prospective, randomized, open-label, blinded end-point (PROBE design) pilot clinical trial is being performed. Patients are eligible for the trial if they have PD dementia (PDD), are able to provide informed consent, and experience disabling motor response fluctuations, bradykinesia, dyskinesia, or painful dystonia, despite optimal pharmacological treatment. In total 44 patients will be randomized to either STN-DBS accompanied by best medical treatment (DBS group) or to best medical treatment alone (BMT group). The primary outcome measure is the change from baseline to 30 weeks on the Movement Disorder Society—Unified Parkinson’s Disease Rating Scale part III score in a standardized off-drug phase. The main secondary outcome measures consist of scales assessing cognitive aspects of daily living, neuropsychiatric symptoms and impulsive compulsive disorders. Additional secondary outcome measures include motor signs during on-drug phase, dyskinesia, motor fluctuations, cognitive performance, (severe) adverse events, treatment satisfaction, and caregiver burden. Patients will be followed during 52 weeks after randomization.

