### Outcome measures and assessment scales

#### Primary outcome measures

The primary outcome is the change from baseline to 30 weeks after randomization in MDS-UPDRS part III off-drug phase [24] compared between the DBS group and the BMT group.

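### The primary outcome is defined and sized as change from baseline, but the analysis section tests the week-30 score without baseline, so the stated 80% power is not that of the stated test

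*Protocol article*

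**What the plan says.** Three places in the protocol article treat the primary outcome as a change. The abstract (Methods) has "The primary outcome measure is the change from baseline to 30 weeks on the Movement Disorder Society", and the scale meant is the off-drug MDS-UPDRS part III. The section Primary outcome measures has "The primary outcome is the change from baseline to 30 weeks after randomization in MDS-UPDRS part III off-drug phase". The section Sample size calculation claims "80% power to detect a difference in mean change scores of 15 points on the MDS-UPDRS part III". The spread behind that figure is given there in the words "assuming that the common standard deviation is 15", and the planned comparison is a two-sample t-test at the two-sided 5% level.

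The section Statistical analysis names a different variable: "The primary outcome - the MDS-UPDRS part III score in off-drug phase at week 30 - will be analyzed using the two-group t-test". Baseline enters only in the sentence that follows: "Additionally, the treatment effects on the MDS-UPDRS follow-up scores will be analyzed, using multivariable linear regression, including the baseline MDS-UPDRS scores into the model".

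**The concern.** A score at week 30 and a change to week 30 are different variables with different standard deviations. A sample size worked out for one does not give the power of a test on the other. Nothing in the article says that the t-test is applied to change scores. Because baseline is brought in separately by the next sentence, the natural literal reading is a t-test that ignores it.

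Two things are at stake. First, the published text gives two definitions of the variable on which the trial will be judged. The promised statistical analysis plan would have to choose between them in an open-label trial, and the article requires that plan only before the database is finalized and locked. Second, there is a loss of precision. The Randomization section plans 44 patients without stratification, so chance differences in baseline severity are left to the analysis. The unadjusted week-30 comparison does nothing about them, and the model that does is placed second.

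**Working it through.** **Inputs from the article.** Difference 15 points; common SD 15, in context the SD of change scores; two-sided 5%; two-group t-test; 17 per arm analysed; 20% attrition; 22 per arm randomised.

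**Assumptions not in the article.** Correlation r between baseline and week-30 scores, varied from 0.3 to 0.8; equal variances at the two times.

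**Step 1: the plan's own figure.** The noncentrality is 15 / (15 × √(2/17)) = 2.915 with 32 degrees of freedom. The noncentral t distribution gives power 0.807 at 17 per arm and 0.781 at 16, so 17 is right. Attrition: 17 / 0.8 = 21.25, rounded up to 22 per arm, 44 in total. The sample size is correct for a t-test on change.

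**Step 2: the SDs of the three analyses.** With the SD of change held at 15:

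- SD of change = SD of score × √(2(1 − r)), so SD of score = 15 / √(2(1 − r)).
- Residual SD after baseline adjustment = SD of score × √(1 − r²), with 31 degrees of freedom.

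Example at r = 0.7: SD of score = 15 / √0.6 = 19.36; residual SD = 19.36 × √0.51 = 13.83.

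**Step 3: power at 17 per arm for a 15-point difference.** The last column multiplies the variance of the adjusted estimate by about 1 + 1/30, the expected cost of chance baseline imbalance at this size.

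| r | SD of score | t-test, week-30 score | t-test, change | Residual SD | Adjusted regression | Adjusted, with imbalance cost |
|---|---|---|---|---|---|---|
| 0.3 | 12.68 | 0.917 | 0.807 | 12.09 | 0.938 | 0.931 |
| 0.4 | 13.69 | 0.872 | 0.807 | 12.55 | 0.921 | 0.913 |
| 0.5 | 15.00 | 0.807 | 0.807 | 12.99 | 0.903 | 0.894 |
| 0.6 | 16.77 | 0.715 | 0.807 | 13.42 | 0.884 | 0.874 |
| 0.7 | 19.36 | 0.591 | 0.807 | 13.83 | 0.865 | 0.854 |
| 0.8 | 23.72 | 0.432 | 0.807 | 14.23 | 0.845 | 0.834 |

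The two t-tests cross at r = 0.5, where √(2(1 − r)) = 1. Above it the week-30 test falls below plan; below it that test exceeds plan. For 80% power the week-30 test needs 13, 15, 17, 21, 28 and 41 per arm down the table.

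**Step 4: the other reading of the SD.** If 15 is the SD of the week-30 score, the week-30 t-test has power 0.807 whatever r is. The adjusted regression then has 0.841 at r = 0.3 rising to 0.997 at r = 0.8 (0.830 to 0.996 with the imbalance cost), again above the week-30 test.

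**Step 5: size of chance imbalance.** The standard error of the baseline difference between arms is SD × √(2/17). At r = 0.5 this is 15 × 0.343 = 5.1 points, about a third of the 15-point target; at r = 0.7 it is 19.36 × 0.343 = 6.6 points.

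**The case against.** The strongest reply is that the sentence is loose shorthand. Its subject is the primary outcome, already defined as change, and the sample size section specifies the same t-test on change scores. On that reading the test and its power agree and no power is lost. The reading is possible and cannot be excluded, but the words name the week-30 score, and a reader should not have to guess which variable was meant.

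A second reply is that the promised statistical analysis plan will settle the matter. That would answer an omission. Here the article has already fixed a variable and a test, and they conflict with its own definition.

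A reader might infer several stronger things that the article does not support:

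- That the trial is underpowered. This needs r above about 0.5 and 15 read as the SD of change. The article gives no r and does not label the SD explicitly.
- That the week-30 comparison is biased. Under randomisation the differences in week-30 score and in change have the same expectation, and the t-test keeps its type I error.
- That there is no order between the two analyses. The t-test is attached to the primary outcome and the regression is introduced as additional, which is an order.
- That adjustment wins at every correlation. With the imbalance cost it is marginally behind the week-30 test at r = 0 (0.975 against 0.979) and behind the change test at r = 0.95 (0.803 against 0.807).
- That the secondary outcomes share the fault. For these the article refers only to appropriate parametric and nonparametric methods, detail that can be left to the statistical analysis plan.

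**Conclusion.** The contradiction is real: the variable named in the Statistical analysis section is not the one defined in the abstract and in Primary outcome measures, nor the one on which the trial was sized. The sample size arithmetic is correct, but read literally its 80% does not describe the stated test. Under equal variances and SD 15 for change, the power of that test could be anywhere from 92% (r = 0.3) to 43% (r = 0.8), and it is below plan only for r above about 0.5. Under either of the milder readings, shorthand for change or 15 as the SD of the score, it is about 81%. This is a fault of consistency and precision, not of validity.

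The order of the analyses is a separate matter of efficiency. With SD 15 for change, the baseline-adjusted regression has about 93% to 83% power over r = 0.3 to 0.8, above both t-tests throughout. Against a t-test on change, a valid and correctly sized test, the gain is about 3 to 9 points for r between 0.8 and 0.5, and 12 points at r = 0.3. Naming one primary variable is necessary; promoting the adjusted model is a free improvement that also does that job.

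**What to change.** In the Statistical analysis section, make one analysis primary: linear regression of the week-30 off-drug MDS-UPDRS part III score on treatment group and baseline score, reporting the treatment coefficient with its 95% confidence interval. With baseline in the model, that coefficient is the same whether the dependent variable is the week-30 score or the change, because subtracting baseline alters only the baseline coefficient. The definition, the sample size and the analysis then agree. Keep a two-group t-test on change from baseline, the test on which the trial was sized, as a supportive analysis. State in Sample size calculation that 15 is the SD of change scores, if that is what was meant.

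The cost is wording and one degree of freedom. The model is already planned and the baseline is already collected, so no new data or patients are needed. The change should be made before any outcome data are examined.

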#### Data safety analysis

As additional risks are associated with this trial, a data safety monitoring board (DSMB) will be established. This committee is independent and has no conflict of interest with the sponsor of the study. During the trial DSMB meetings will be held two months after the fifth, tenth and fifteenth patient in the DBS group have undergone surgery. During these meetings relevant baseline data, study performance data, secondary outcome data and safety data will be analysed and reviewed. Primary outcome data will not be reviewed. Since the interim analysis concerns an analysis for safety in a small sample, no pre-specified formal statistical stopping rule for safety is formulated.

## Discussion

A pilot trial investigating the motor efficacy as well as cognitive and psychiatric outcomes of DBS for patients with PDD is necessary and timely. Currently, patients with PD and disabling motor symptoms who are also suffering from dementia are not considered for DBS. This concerns a relatively large group of patients and there are no appropriate scientific data underpinning this clinical practice. If motor function improves in PDD patients, these patients may also experience significant improvement in their QoL, there might be less burden of care and patients might even be able to live longer at home instead of in a nursing home.

Some aspects related to the study design warrant discussion. First is the study design. In order to investigate the clinical usefulness of STN-DBS in PDD, a large clinical trial is needed. However, it is unknown what the inclusion rate will be and whether these patients are able to complete such a trial. It would also be unethical to perform such a large trial before the motor benefit of DBS in PDD has been confirmed. As PDD patients constitute a vulnerable population, we aim to first assess the motor efficacy of DBS, which is the scope of this trial. All outcomes in this single-center pilot trial will be helpful for the realization of future trials of DBS in this patient population. Second, neither patients nor the referring treating neurologist can be blinded to treatment allocation. A sham surgery would be unethical. DBS surgery is an invasive procedure and patients randomized to the sham surgery would be exposed to operative risks with no possibility of benefit. Similarly, a study design where DBS is implanted in all patients, but not activated until after the trial for patients in the control group, is for the same reason not possible. Furthermore, hippocampal atrophy with brain MRI, which would suggest Alzheimer’s disease as a cause for the dementia, was not an exclusion criterion for the trial. For all patients, the PDD diagnosis according to MDS clinical diagnostic criteria was established by means of a full neuropsychological examination. Lastly, for the main secondary outcome the composite outcome measure will be used. This is not a validated outcome measure. However, the composite outcome improves the ability to detect differences in cognitive function and psychiatric symptoms between the BMT group and DBS group.

In conclusion, we have developed a protocol for a prospective, randomized, open-label pilot trial comparing motor efficacy and safety of STN DBS and BMT in patients with PDD. With the proposed study, we aim to investigate whether STN-DBS is an effective treatment for motor symptoms in PDD patients, like it is the case in non-demented PD patients. Whether this motor improvement outweighs surgical, cognitive and psychiatric safety is an exploratory outcome and might need to be assessed more extensively in a larger trial.

## Data Availability

Depending on the type of data and associated privacy regulations, data from the DBS-MODE project will be made publicly available or will become available via the corresponding author, upon reasonable request.

## Abbreviations

A-IADL-Q-SV: Amsterdam iADL questionnaire – short version
ALDS: Academic Medical Center Linear Disability Score
BMT: Best oral medical treatment
CDRS: Clinical Dyskinesia Rating Scale
CGI-C: Clinical Global Impression of Change
DBS: Deep brain stimulation
DSM-5: Fifth edition of the Diagnostic and Statistical Manual of Mental Disorders
DSMB: Data safety monitoring board
ICD: Impulse control disorder
MCI: Mild cognitive impairment
MDS: Movement Disorder Society
MoCA: Montreal Cognitive Assessment
MRS: Modified Rankin Scale
NPI-Q: Neuropsychiatric Inventory Questionnaire
PD: Parkinson’s disease
PDD: Parkinson’s disease dementia
PROBE: Prospective, randomized, open-label, blinded end-point
QoL: Quality of life
QUIP: Questionnaire for Impulsive Disorders in Parkinson’s Disease
(S)AEs: (Serious) adverse events
STN: Subthalamic nucleus
UPDRS: Unified Parkinson’s Disease Rating Scale
